### Randomization

With the help of the computer software Research Randomizer [55], a block randomization has been conducted by the Study Centre of Mental Disorders. Stratified according to the four clinics to achieve an equal share of intervention and control groups, the lists have been assigned to the trial sites by a researcher not involved in the study.

### Statistical methods

For the primary analyses, analysis of covariance will be used to compare SIBAR risk scores 12 weeks after the discharge of inpatient rehabilitation (T2) between the internet-based aftercare program (intervention group) and the control group, with covariates for rehabilitation clinic and baseline SIBAR risk score (T1). Cohen’s effect sizes will be calculated. Intention to treat analyses as well as completer analyses will be conducted. Replacement strategies of missing values will be discussed after assessing the pattern of the missing value structure.

For the secondary analyses, self-report questionnaires (AVEM-44; Patient Health Questionnaire; Generalized Anxiety Disorder 7-item Scale; Short-Form 12-item Health Survey; Berlin Social Support Scale; Helping Alliance Questionnaire) will be analyzed by mixed models with repeated measurements. It is expected that the SIBAR risk score and the other self-report measures will not be linear across time. Therefore, these measures will be evaluated by a linear model with fixed effects for treatment and rehabilitation center and time. There will be an indicator variable for the post treatment measurements and the SIBAR risk score at baseline will serve as a covariate. All analyses will be conducted on a two-sided level of significance of α = 0.05.

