### Interventions

At inpatient admission, patients are informed in detail about the study by the clinical staff of the rehabilitation centers. After giving written consent and screening, the eligible patients are assembled into a group of up to 12 (minimum of two) participants. Over a period of two to three weeks, participants are trained in stress perception and management by four interactive psycho-educative, cognitive-behavioral and psychodynamic modules (90 minutes each). To standardize the procedure, the staff has been trained using a comprehensive manual in a detailed one-day seminar before study start, with a refresher half-way through recruitment. In the first part of the fourth module, the participants are familiarized with the three components of Luborsky’s Core Conflictual Relationship Theme and its recurrent and potentially mal-adaptive nature, focusing on typical expectations regarding return to work [43,44]. This approach also serves as a basis for the upcoming writing task in the intervention group. The introduction to the features of the internet platform, given in the last of four inpatient GSA modules, differs between the two randomized arms. Up to the fourth session, participants and trainers are blind to the result of randomization. Immediately prior to the fourth module, the trainer is unblinded. In the second part of the fourth session, all participants are introduced to the special features of the internet platform. Instructions for participants depend on the arm they are randomized to (intervention versus control). Because there is plenty of interaction between consecutive cohorts of patients admitted to medical rehabilitation, we do not randomize individuals but groups of eligible patients. With this cluster randomization, we aim to minimize contamination through the interaction of patients during inpatient rehabilitation who are getting different instructions for the aftercare interventions in the two randomized arms.

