### Sample size calculation

At present, there are no reports of reliable effect sizes for internet-based interventions aiming at the improvement of vocational strains through online aftercare interventions. We therefore made conservative calculations with an expected small to moderate effect size (d = 0.30), a statistical power of 0.80 and alpha of 0.05. A total sample size of n = 190 will be necessary to gain significant results (calculation with GPower 3.0.10 for analysis of variance with fixed effects, special, main effects and interactions).

Patients are randomized in clusters - the cluster size is set at two to twelve participants. For each clinic, 30 blocks have been generated, each consisting of both groups in random order. Altogether, there is a maximum of 60 clusters per clinic with an equal share of intervention and control groups. To adjust sample size calculation for clustering, we multiplied the needed sample size by the design effect (1+(m-1)ρ, with m = average cluster size and ρ = intracluster correlation coefficient) as suggested in the CONSORT statement extension for cluster randomized trials [53]. With an anticipated average cluster size of six participants and an intracluster correlation coefficient of ρ = 0.30, as reported by Campbell *et al*. for comparable studies [54], we calculated a design effect of 2.5. By multiplying our needed sample size of n = 190 with the design effect we get a minimum sample size of n = 475 needed for robust statistical analyses. Even in case of a dropout rate of 40% as reported in a recent aftercare study [21], the anticipated number of n = 800 (n = 100 per clinic and condition) will provide statistically confirmed data.

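### The primary ANCOVA has no term for the randomised group, so at the plan's own ICC its nominal 5% test runs at about 14–25%

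*Protocol article*

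**What the plan says.** The Interventions section explains that, to limit contamination between patients who meet during their stay, "we do not randomize individuals but groups of eligible patients". The randomised unit is therefore the GSA training group. The Sample size calculation section gives its dimensions: "the cluster size is set at two to twelve participants", with a mean of six and "an intracluster correlation coefficient of ρ = 0.30". On that basis "we multiplied the needed sample size by the design effect", which is 2.5 and takes the required total from 190 to 475. Recruitment is set at 800 to allow for 40% dropout. Randomisation is stratified by the four clinics, with up to 60 groups in each.

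Under Statistical methods the primary model is: "analysis of covariance will be used to compare SIBAR risk scores 12 weeks after the discharge of inpatient rehabilitation (T2") between the arms, "with covariates for rehabilitation clinic and baseline SIBAR risk score (T1"). The randomised group appears neither as a random effect, nor as the cluster for the standard errors, nor as the unit of analysis. For the secondary outcomes the section speaks of repeated-measures mixed models and then states that "these measures will be evaluated by a linear model with fixed effects for treatment and rehabilitation center and time", together with a post-treatment indicator and the baseline SIBAR score. Again no group term is named. The Discussion brings in patient category and centre as further analysis variables, but not the group.

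**The concern.** Patients trained together are expected to resemble one another, and the sample size section makes that expectation explicit. An ANCOVA with arm, clinic and baseline score counts each patient as a separate piece of evidence on the treatment effect, although the arm was assigned to whole groups. The clinic covariate removes differences between clinics. It leaves the correlation among members of the same group within a clinic, and that is the correlation for which the sample size was raised.

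Recruiting more patients does not cure this. The inflation protects power if the analysis accounts for clustering. It does not protect the type I error, because the naive standard error stays too small by the same ratio at any sample size. At stake is the confirmatory test: p-values too small, intervals too narrow, and a significant primary result that could be chance far more often than the stated 5%.

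**Working it through.** **Inputs.** From Sample size calculation: mean group size m = 6, ICC ρ = 0.30, sizes 2 to 12, dropout 40%, unadjusted total 190, planned total 800. From Statistical methods: two-sided α = 0.05 and the ANCOVA terms above.

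**The plan's own figures.** Design effect DE = 1 + (m − 1)ρ = 1 + 5 × 0.30 = 2.5, and 190 × 2.5 = 475. Allowing for dropout, 475 / 0.60 = 792, against 800 planned. These reproduce.

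**Error of a test that ignores groups.** The naive standard error is too small by a factor √DE, so under no treatment effect the actual error is 2 × [1 − Φ(1.96/√DE)]. For unequal group sizes with coefficient of variation CV, DE = 1 + [(1 + CV²)m − 1]ρ.

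The document gives no CV, so I assume 0.45–0.50. For scale, sizes spread evenly over 2–10 have mean 6 and CV √(80/12)/6 = 0.43; over 2–12 they have mean 7 and CV √10/7 = 0.45. After 40% dropout the mean analysed group is 6 × 0.60 = 3.6.

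| Setting, ICC 0.30 | DE | 1.96/√DE | Actual error |
|---|---|---|---|
| 6 per group, equal sizes | 2.50 | 1.240 | 21.5% |
| 3.6 per group, equal sizes | 1.78 | 1.469 | 14.2% |
| Mean 6, CV 0.45 | 2.865 | 1.158 | 24.7% |
| Mean 6, CV 0.50 | 2.95 | 1.141 | 25.4% |

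At DE 2.5 the naive interval has 1/√2.5 = 63% of the correct width.

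**Simulation of the stated ANCOVA.** Four clinics, about 800 patients, groups allocated in blocks of two, no treatment effect, terms for arm, baseline and clinic, and dropout at random. The ICC is the one remaining after those covariates. There were 4,000 runs per setting, so the Monte Carlo standard error near 20% is √(0.2 × 0.8/4000) = 0.6 points. Each cell gives rejection with full follow-up / with 40% dropout.

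| Group sizes | ICC 0.30 | ICC 0.10 (assumed) | ICC 0.05 (assumed) |
|---|---|---|---|
| All 6 | 20.0% / 15.5% | 11.8% / 8.2% | 8.7% / 6.7% |
| 2–10, mean 6 | 24.2% / 17.3% | 11.3% / 9.7% | 7.9% / 7.1% |
| 2–12, mean 7 | 27.3% / 20.4% | 13.7% / 9.6% | 8.7% / 7.9% |

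**Sensitivity to the ICC by formula**, from 3.6 per group with equal sizes to mean 6 with CV 0.45: 6.5–8.7% at ICC 0.05, 8.1–12.4% at 0.10 and 11.2–19.1% at 0.20.

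**Does accounting for the group help?** In a similar simulation at ICC 0.30 (1,500 runs per setting, sizes 2–10), cluster-robust standard errors gave 6.0% with full follow-up and 6.7% with 40% dropout. A generalised least squares analysis with a random group effect and the true ICC supplied gave about 4–5%. A mixed model with estimated variances and Kenward-Roger or Satterthwaite degrees of freedom was not simulated.

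**The case against.** - **It is a short journal summary.** The error structure is often left to an analysis plan, and the authors plainly knew the design was clustered. This would carry weight had the article only named a method. It names the model and its covariates, includes the stratum and leaves out the cluster. Followed as written, that gives the wrong standard error.
- **The ICC of 0.30 is a planning value.** It is not stated to be the correlation of the T2 score after adjustment. The baseline covariate is taken at T1, after the inpatient training, and may absorb part of the group effect. The later writing task and therapist feedback are individual. A lower residual ICC is plausible, though the document gives no figure. This stands as a limit on the size. It does not bring the error back to 5%.
- **The 25% end is conditional.** It needs full follow-up and an assumed spread of sizes. With 40% dropout, simulated rejection at mean size six was 15.5–17.3%. This also stands.
- **The secondary analysis is called a mixed model.** It may therefore handle correlation within a patient, and listing fixed effects does not rule out a random group effect. For that model the point is narrower: no group term is named, and the 14–25% was not computed for it.
- **The extra patients are not wasted.** They carry real information whatever standard error is used. What fails is the validity of the test.

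**Conclusion.** The concern holds and must be fixed, because it affects the confirmatory test of the primary outcome. At the plan's own ICC of 0.30 the stated ANCOVA has a true error of about 14–25% in place of 5%, roughly three to five times the claim, with 21.5% at the plan's own design effect. The lower end assumes equal groups thinned by 40% dropout. The upper end assumes full follow-up and a group-size CV of about 0.45–0.50. All of these figures take 0.30 as the correlation left after adjustment for clinic and baseline. The direction of the error does not depend on that value: any positive correlation within groups pushes the rate above nominal.

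**What to change.** Replace the primary ANCOVA with a linear mixed model for the T2 SIBAR risk score: fixed effects for arm, clinic and baseline SIBAR score, and a random intercept for GSA group, with Kenward-Roger or Satterthwaite degrees of freedom. Keeping the ANCOVA with small-sample-corrected cluster-robust standard errors, clustered on GSA group, is an acceptable alternative. The choice between them matters less than fixing one before the data are analysed. State the same group random intercept in every secondary model that compares the arms, in addition to whatever handles repeated measurements within a patient. Report the estimated ICC with its confidence interval.

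The cost is one sentence in the analysis section and a standard routine. At six per group, 800 patients form about 133 groups (800/6), enough to estimate the group variance. Group membership must be in the analysis file; nothing changes in design, recruitment or assessment. Intervals will be wider than the naive ones, by a factor of √2.5 = 1.58 at the plan's design effect or √1.78 = 1.33 after 40% dropout. That is the honest width for this design.

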One of the other challenges of the study seems to be the lack of immediate interaction, which presumably requires more incentives for the participants than in face-to-face interactions [58]. It remains to be seen whether the computer-generated feedback following each completed online questionnaire in both randomized arms will serve as a sufficient incentive.

One restriction is that not all rehabilitation centers have the resources for online assessments during inpatient rehabilitation, specifically for an introduction to the internet platform. Following the review of Wantland and colleagues [40], we assume the online and paper-pencil collected data vary little in reliability and validity, although bias caused by the different ways of data collection cannot be excluded completely [59,60]. However, we cannot completely preclude that filling out questionnaires online during inpatient rehabilitation may increase participation in our program. We will therefore compare the frequency of utilization between those who fill out baseline questionnaires online and offline. Furthermore, we have to expect that missing out on an introduction to the internet platform in practice during inpatient rehabilitation is leading to a higher rate of patients dropping out of the study. Therefore, the rehabilitation center will be an important covariate in the statistical analyses.

By evaluating our online intervention comprehensively, we aim to estimate the short-term and especially the long-term effects of the program on stress management and coping concerning job strain and, finally, on successful occupational reintegration.

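### The missing-data method for the primary T2 comparison is to be settled only after the missing-value pattern is known, and no analysis set is named as decisive

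*Protocol article*

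**What the plan says.** In the Protocol article, Statistical methods, the primary analysis is an analysis of covariance of the SIBAR risk score at T2, with clinic and the T1 score as covariates. On analysis sets the section says: "Intention to treat analyses as well as completer analyses will be conducted". It does not rank the two or define a completer. On missing values it says: "Replacement strategies of missing values will be discussed after assessing the pattern of the missing value structure". It names no method or fallback. It does not say whether the people assessing the pattern will be blind to arm and outcome, or whether the choice will come before any comparison of the arms.

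The next paragraph of that section gives repeated-measures mixed models for the secondary questionnaires and a linear model over time that also covers the SIBAR score. Neither is assigned to the primary T2 comparison.

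Three other places bear on the point:

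- **Sample size calculation** allows for substantial loss: "Even in case of a dropout rate of 40% as reported in a recent aftercare study", it says, "the anticipated number of n = 800 (n = 100 per clinic and condition) will provide statistically confirmed data".
- **Discussion** expects that having no hands-on introduction to the platform is "leading to a higher rate of patients dropping out of the study", and answers this by making the rehabilitation center a covariate.
- **Assessment** provides that patients who do not respond online within two weeks are mailed a paper questionnaire.

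**The concern.** The text goes further than leaving a detail open. It sets an order: the missing-value pattern is looked at first, and the replacement method is discussed afterwards. Because the primary model uses a single time point, patients without a T2 score drop out of it unless a value is supplied. The completer analysis can therefore be run as written, but the intention-to-treat analysis cannot. If the two later disagree, nothing in the plan says which is the trial's result.

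Missingness linked to arm is plausible. Patients know their allocation, and the arms differ in contact: weekly individual feedback in one, six reminder e-mails in the other.

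Timing adds some weight. Trial status expects the last follow-up by September 2013, and T3 falls nine months after T2. The last T2 assessments would then fall around December 2012, before the article's publication date of 25 January 2013. This is an inference from the planned dates. It does not show that anyone had looked at the data.

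**Working it through.** **1. The plan's own figures (Sample size calculation).** The unclustered total of 190 is taken as given; whether it follows from d = 0.30 is a separate question.

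- Design effect: 1 + (6 − 1) × 0.30 = 2.5, as stated.
- Clustered minimum: 190 × 2.5 = 475, as stated.
- Allowing for 40% dropout: 475 / (1 − 0.40) = 791.7, so 792, against 800 planned.
- Remaining at 40% dropout: 800 × 0.60 = 480, which is at least 475. Missing: 800 × 0.40 = 320.

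The arithmetic reproduces. In the worst case that the plan provides for, 320 of 800 primary values are absent.

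**2. What can be run from the text.**

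| Analysis | Needs | Defined in the article? |
|---|---|---|
| Completer ANCOVA at T2 | observed T2 and T1 scores | yes, apart from the meaning of completer |
| Intention-to-treat ANCOVA at T2 | a T2 value for every randomised patient | no, until the deferred choice is made |

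**3. Illustration: effect in the missing patients.** Assume 40% missing in each arm and a benefit of 0.30 SD among completers. With effect e in the missing, the overall effect is 0.6 × 0.30 + 0.4 × e:

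| e (assumed) | Overall effect |
|---|---|
| 0.30 | 0.30 |
| 0.15 | 0.24 |
| 0 | 0.18 |
| −0.30 | 0.06 |

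**4. Illustration: departure from missing at random.** If intervention dropouts are worse off, relative to control dropouts, than missing at random implies, by 0.1 to 0.3 SD, the bias is 0.4 × 0.1 = 0.04 to 0.4 × 0.3 = 0.12 SD. Against the planned d = 0.30 that is 0.04 / 0.30 = 13% to 0.12 / 0.30 = 40%.

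**5. Illustration: effect of the method alone.** The T2 ANCOVA was simulated with 800 patients, 40% missing completely at random, an assumed T1–T2 correlation of 0.5 and no clustering.

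- With a true effect of 0.30, the completer estimate averaged 0.30 and carrying T1 forward gave 0.18. The second figure also follows directly: a carried-forward score, once adjusted for T1, holds no arm difference, so 0.6 × 0.30 + 0.4 × 0 = 0.18.
- With no effect (6,000 runs), each analysis alone rejected in about 5.0% of trials. Claiming success if either was significant rejected in about 6.6%. Two independent tests would give 1 − 0.95² = 9.75%.

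The effect in the missing, the 0.1–0.3 SD shift, the correlation and the carry-forward method are all assumptions. The article gives none of them.

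**The case against.** The strongest reply is that a journal article condenses a fuller protocol, and that imputation methods and the ranking of analysis sets usually sit in the analysis plan. That would answer a complaint of silence. It does not answer a sentence that places the choice after the data have been inspected. The other objections limit the point and largely stand:

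- **Outcomes seen.** A reader might infer that the method will be picked with outcomes in view. The text speaks only of the pattern of missing values, which can be reviewed blind, and such a review is ordinary practice. What is missing is a statement that it will be blind.
- **Equal standing.** A reader might infer that the two analyses rank equally. The text merely omits a ranking, and it names intention to treat first.
- **40% missing.** This is a stress-test figure taken from another aftercare study, not the expected rate. Paper questionnaires go to online non-responders, so leaving the program does not mean a missing T2 score.
- **Dropout by clinic.** Randomisation is stratified by clinic and clinic is a covariate, so loss driven by clinic alone is adjusted for. The concern is loss that differs by arm and outcome.
- **Completers without a counterpart.** A reader might infer that intervention completers have no comparable controls. That holds only if completer means finishing the program. If it means returning the questionnaire, such patients exist in both arms.
- **T3 ignored.** The plan does analyse T3. It only leaves T3 out of the primary comparison.

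**Conclusion.** The point holds as one of pre-specification. The method that defines the intention-to-treat result is to be chosen after trial data are available, with no promise of blinding, and no analysis set is named as decisive. The primary estimate can therefore depend on a later choice.

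Under the assumptions shown, the estimate could move from 0.30 to 0.18 SD, and the type I error could rise from 5% to about 6.6% if either of two analyses could be claimed. The documents do not support the stronger reading that control of the 5% level is lost, and none of these figures predicts what this trial will show. The planned 800 is not made wrong by this point. The wording should be corrected before analysis, because the correction is cheap and cannot be made credibly afterwards.

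**What to change.** Before any T2 comparison by arm:

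1. State that the intention-to-treat analysis of all randomised patients decides. Define completer (program or questionnaire) and label that analysis supportive.
2. Name one primary method. One option is a likelihood-based mixed model of the post-treatment SIBAR scores (T2 and T3), with the T2 contrast as primary, clinic and the T1 score as covariates (as the plan already has), and random effects for GSA group and patient. Another is multilevel multiple imputation under a stated missing-at-random assumption. The two are not interchangeable if imputation adds variables such as log-in data, because that changes the assumption. A patient with neither T2 nor T3 adds nothing to the mixed model, so the assumption for such patients should be written down.
3. Keep the GSA group in whichever method is chosen. The sample size assumes an intracluster correlation of 0.30, but the stated ANCOVA has no cluster term.
4. Add a delta-adjusted sensitivity analysis, for example with intervention dropouts 0 to 0.3 SD worse than missing at random implies.
5. Replace the sentence that defers the choice. Any remaining review of missingness should be blind to arm and outcome.

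The cost is plan wording and a little more programming, and possibly wider intervals. No new data are needed and the planned sample size stays at 800.

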### Assessment

As shown in Figure 1, the time points of assessment by self-rating scales are at the beginning (T0) and the end (T1) of inpatient rehabilitation, at the end of the aftercare (T2 = 3 months after T1) and 9 months later (T3 = 12 months after T1). Additional somatic and psychological measures, documented during inpatient rehabilitation, are assessed at T1.

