### Objectives and hypotheses

In this study we evaluate the acceptance and efficacy of an internet-based aftercare program for three different indications of medical rehabilitation (at the participant level), with the following hypotheses:

1. We expect that taking part in the internet-based aftercare program helps stabilize the improvements achieved during inpatient rehabilitation concerning stress management and coping with conflicts at the workplace. Therefore, participants of the intervention will have a lower risk for premature pension than the control group.

2. We expect these effects to persist up to 9 months after the end of the internet-based treatment.

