### Outcomes

The primary outcome measure is a risk factor for early pension, measured by the screening questionnaire SIBAR, a score ≤8 indicating a decreased risk for premature pension. The primary endpoint will be the assessment at the end of the internet-based treatment (T2, that is, 3 months after inpatient rehabilitation). Secondary outcome measures include the subjective prognosis for work and capability, also measured by the SIBAR, and scales for the work-related behavior and experience pattern (AVEM-44 [45]), physical and mental health (Patient Health Questionnaire [47], Generalized Anxiety Disorder 7-item Scale [48], Short-Form 12-item Health Survey [49]), social support (Berlin Social Support Scale [50]), therapeutic alliance (Helping Alliance Questionnaire [51], Helping Alliance Questionnaire II [52]) and self-developed items measuring patients‘ satisfaction with the aftercare program. Long-term effects of the primary outcome measure will be analyzed 9 months after termination of the internet-based aftercare at T3. Except for the Helping Alliance Questionnaires, only applied in the intervention group, all instruments are used in both randomized arms.

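### The repeated-measures model has no treatment-by-time term, so its one pooled treatment coefficient cannot show whether the effect persists at T3 (hypothesis 2)

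*Protocol article*

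**What the plan says.** All references are to the protocol article.

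- **Objectives and hypotheses.** There are two hypotheses. The first is a lower risk of premature pension in the intervention group. The second concerns duration: "We expect these effects to persist up to 9 months after the end of the internet-based treatment".
- **Assessment.** T1 is the end of inpatient rehabilitation, T2 is 3 months after T1 (end of aftercare), and T3 is 12 months after T1.
- **Outcomes.** The primary endpoint is at T2. For T3 the section says: "Long-term effects of the primary outcome measure will be analyzed 9 months after termination of the internet-based aftercare at T3". It names no method.
- **Statistical methods, primary analysis.** An ANCOVA of the SIBAR risk score at T2, with clinic and the T1 score as covariates. No matching analysis at T3 is given.
- **Statistical methods, secondary analyses.** Mixed models with repeated measurements. The text first states: "It is expected that the SIBAR risk score and the other self-report measures will not be linear across time". It then draws the consequence that "these measures will be evaluated by a linear model with fixed effects for treatment and rehabilitation center and time", and adds: "There will be an indicator variable for the post treatment measurements and the SIBAR risk score at baseline will serve as a covariate". The measures referred to include the SIBAR risk score itself. No term is said to be crossed with treatment, and the section does not list which occasions are responses.

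**The concern.** Persistence is a statement about the treatment effect at a particular time. A model with treatment and time as main effects assumes that the difference between the arms is the same at every occasion in the response. It then reports one number for that difference, so the assumption that hypothesis 2 is meant to test is built into the model.

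This matters because the repeated-measures model is the only described analysis that reaches T3. If the T3 question were answered from its treatment coefficient, a benefit present at the end of aftercare and gone nine months later could be read as a lasting effect of moderate size. A benefit that appeared only late would look the same.

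**Working it through.** **Inputs.** From the documents: the model terms (Statistical methods), the occasions T0 to T3 (Assessment), and d = 0.30 as the planning effect size (Sample size calculation). Assumed: the pattern of effects over time, complete data, and equal correlation between occasions (0.5 in the calculation). The plan states no figure that could be reproduced here.

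**Step 1: what the treatment coefficient estimates.** Write the arm difference at occasion t as Δ(t). In expectation, randomisation balances centre and the baseline covariate between the arms. With categorical time and no interaction, generalised least squares estimates Σ w(t)Δ(t), with weights proportional to V⁻¹1, where V is the within-person covariance matrix. Under equal variances and correlations the weights are equal, so the coefficient is the plain mean of Δ(t) over the occasions in the response.

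**Step 2: numbers.** Δ is 0 at T0 and T1.

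| Assumed effect at T2, T3 | Responses T2, T3 | T1 to T3 | T0 to T3 | With treatment-by-time: T2, T3 |
|---|---|---|---|---|
| 0.30, 0.30 (persists) | 0.30 | 0.20 | 0.15 | 0.30, 0.30 |
| 0.30, 0.15 (halved) | 0.225 | 0.15 | 0.113 | 0.30, 0.15 |
| 0.30, 0 (lost) | 0.15 | 0.10 | 0.075 | 0.30, 0 |
| 0, 0.30 (late only) | 0.15 | 0.10 | 0.075 | 0, 0.30 |

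For the lost effect: (0.30 + 0)/2 = 0.15. For the late effect: (0 + 0.30)/2 = 0.15. The two rows agree in every column without the interaction. With the interaction, the T3 effect is recovered in each scenario.

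**Step 3: dilution, if it applies.** With T1 among the responses, a fully persistent effect gives (0 + 0.30 + 0.30)/3 = 0.20, a loss of one third. With T2 and T3 only, it gives 0.30 and nothing is lost.

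**Step 4: does the post-treatment indicator help?** As a main effect it adds nothing to categorical time. If crossed with treatment, which the text does not say, a single indicator gives one effect for T2 and T3 together. That would remove the dilution from T1 but would still not separate T3 from T2.

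**Step 5: unequal follow-up.** Suppose everyone is seen at T2 and 40% are missing at T3, borrowing the article's overall dropout allowance, with correlation 0.5. Information per participant is (1/0.75)·[[1, −0.5], [−0.5, 1]] for those with both visits and [[1, 0], [0, 0]] for those with T2 only. Combined 0.6 to 0.4, this gives [[1.2, −0.4], [−0.4, 0.8]]. The row sums are 0.8 and 0.4, so T2 has weight 2/3. An effect of 0.30 at T2 and 0 at T3 then returns 0.30 × 2/3 = 0.20, so the pooled figure moves further from the true T3 value.

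**The case against.** The strongest reply has four parts.

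1. **The Outcomes section commits to a T3 analysis of the primary outcome.** A T3 ANCOVA would fit that sentence, and nothing in Statistical methods excludes it. This stands. A reader might infer that the plan as a whole cannot test hypothesis 2, but the documents do not support that: the limitation belongs to the one model described, and the T3 analysis is announced without a method.

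2. **An article condenses, and interactions are often left to a fuller plan.** The text never says main effects only. In part this stands, since a fuller document may add the term. However, the article is not silent on the model. It lists the fixed effects, the indicator and the covariate, and that list does not answer a hypothesis the article states. The reference to main effects and interactions under Sample size calculation names the GPower procedure, not a term of the analysis model.

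3. **Dilution is not established.** A reader might infer that the model understates a real effect by a third. That requires T1 among the responses. The text does not say so, and for SIBAR it is unlikely, because the ANCOVA paragraph defines baseline as T1 and the baseline SIBAR score is the covariate. With T2 and T3 as responses a persistent effect is estimated without loss. Dilution is therefore conditional; pooling over T2 and T3 is not.

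4. **Non-linearity is dealt with.** The article gives the expected non-linear course as its reason for this model, most naturally with categorical time. This is right, and it is no part of the criticism. A flexible time course common to both arms still leaves the arm difference constant.

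**Conclusion.** The point holds for the repeated-measures model as described. It gives one treatment coefficient pooled over T2 and T3 and so cannot distinguish an effect that persists from one that is lost or arrives late. Under assumed effects of 0.30 and 0, in either order, the coefficient is 0.15. The exact value depends on the assumed effects, the correlation and the missing data, but the inability to isolate T3 does not. If T1 is also a response, a persistent 0.30 becomes 0.20; the text leaves this open.

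The scope is limited. The primary ANCOVA at T2 is unaffected and already gives the SIBAR score its own T2 contrast. What is affected is the second of two stated hypotheses, together with the longitudinal analysis of the secondary measures. The plan should be changed on this point, but its primary conclusion is not at risk.

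**What to change.** In Statistical methods:

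- state that T2 and T3 are the responses, with time categorical and the baseline value as covariate (alternatively, include baseline as a response and constrain the arms to a common baseline mean);
- add the treatment-by-time interaction;
- prespecify the arm contrast at T3 from this model as the test of hypothesis 2.

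For the SIBAR score alone, a T3 ANCOVA parallel to the T2 one would also suffice, and would supply the method missing from the Outcomes section.

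The cost is one model term and a sentence or two, with no new data. The T3 contrast rests on one occasion, so it is less precise than the pooled coefficient. As an illustration, take 800 × 0.6 = 480 participants and the article's design effect of 2.5, so 480/2.5 = 192 effective (96 per arm), unit SD, within-person correlation 0.5 (assumed) and no gain from covariates. The standard error is √(2/96) = 0.144 at T3 and √(2 × 0.75/96) = 0.125 pooled. Power for 0.30 is then about 0.55 and 0.67. The pooled test gains that power by answering a different question.
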